### Study groups

All participants will receive one of three interventions during the study. First, when infants are 5.5 months old, a dietary workshop at a private nutrition office equipped with the test kitchen, in which nutritionists will teach parents how to begin CF as appropriate for the group to which they were randomized. Participants and nutritionists will cook example meals together in real-time at the test kitchen (Table 1).

**Table 1 Tab1:**
[figure not shown]
Interventions and outcome measures at specified time points

*BLISS*, Baby-led Introduction to SolidS; *PLW*, Parent-Led Weaning, *CRC*, Clinical Research Center; *CRP*, C-reactive protein; *BEBQ*, Baby Eating Behavior Questionnaire; *CEBQ*, Child Eating Behavior Questionnaire; *CFSQ*, Caregiver Feeding Style Questionnaire; *DEBQ*, Dutch Eating Behavior Questionnaire; *MCH-FS*, Montreal Children’s Hospital Eating Scale; *SLP*, Speech-Language Pathologists

At the same visit, speech therapists will advise on choking prevention, showing videos with examples of choking and gagging. All advice will be standardized; each group will have its own set of printed material of topics to be addressed by the professional, and each participant will receive a copy to take home. The major differences between the intervention groups are the consistency of foods and the level of adult participation during each meal. The basic information that every group will receive during the first intervention is:
Encouragement to breastfeed exclusively for 6 months and continue breastfeeding to at least 24 months or longer.Not to start CF until their infant is 6 months of age.Make sure the infant is always sitting upright and under adult supervision when they are eating.Specific food techniques to improve food bioavailability of iron and energy.Avoid offering honey, sugar, caffeine, juice, processed foods, and low-energy foods, such as soups, in the first 2 years of life.At age 6 months, offer a fruit at two different times plus one main meal (lunch) and, by 7 months, introduce a second main meal (dinner).Not to sift and/or liquefy any type of food.Not to offer hard foods such popcorn or nuts, nor any foods that might become sticky in the mouth, such as peanut butter.

After the first intervention, every mother will receive a dietitian’s personal phone number to call if they have questions related to the study or the CF process.

Second, a home visit at 9 months of age will serve to measure anthropometric parameters of the mother and child. At this time, questionnaires will also be administered and any extra individualized advice or support for the CF process will be provided, always appropriate for the approach to which each mother-child pair was allocated. The visits will be led by two blinded researchers; to avoid unblinding, one will obtain anthropometric measurements before the other applies the questionnaire, as some answers given might reveal the allocation group. The visit will end with a thank-you card, to motivate family engagement with the study.

Finally, the last intervention will be conducted at the HCPA Clinical Research Center (CRC). Blood samples will be drawn for measurement of plasma ferritin, C-reactive protein (CRP), and a complete blood count, as well as saliva for genetic tests. Anthropometric measurements will be repeated, an intraoral examination will be performed, and the end-of-study questionnaires will be administered, as well as a flavor preference test. Mothers will then receive a booklet with advice on healthy nutrition and oral habits, such as nutritional assessment, oral evaluation, and oral hygiene guidance; blood test results; and nutritional guidelines for the child’s further years to come, encouraging them to continue to pay attention to healthy eating.

### Parent-Led Weaning group

Mothers allocated to the PLW group, besides the standard information described above, will be encouraged to spoon-feed pureed foods to their infants, following the traditional feeding method. Consistency should progress gradually until family meal texture is reached by 12 months of age. Mothers will be instructed not to mix or incorporate more than one food at a time, to ensure the child is capable of learning the difference between flavors.

### BLISS group

In addition to the standard information, participants from the BLISS group will be taught to prepare meals shaped into sticks, allowing the child to self-feed without adult interference. The ideal food consistency, size, and shape will be demonstrated during the workshop to guarantee the method is properly performed. Recipes for adaptation of foods such as beans will be given and explored. Although we will not expect the adult to feed the child, we intend to emphasize the difference between not interfering with the feeding process and supervising the child, with an emphasis on the advice to never leave the child alone during a meal.

### Mixed group

This group will be instructed to combine the two methods explored above according to the child’s wishes. In short, the mother would prepare meals in both consistencies and allow the child to both be spoon-fed and grab sticks of food concomitantly as they desire, without following a regular pattern. If the child prefers to eat certain types of foods as sticks and others mashed, that would be allowed, i.e., self-feed fruit sticks and then be spoon-fed dinner. All standard information would also be given to this group.

### Adherence

To ensure the families follow these instructions, a blinded researcher will conduct a phone call when the child is 7 months of age and ask some key questions (about food consistency when the child started to eat, and at 7 months; if the child takes food to mouth alone; and if the child receives food in spoon). A different researcher will analyze the answers and compare them with further data collected at the 9-month visit, in addition to a 24-h dietary record. These records will be collected during the home visit, by trained researchers. However, as some mothers might not be able to quantify food intake exactly, all participants will also be asked when they introduced a variety of different foods at the 9-month and 12-month visits. Questionnaires to assess adherence to self-feeding, breastfeeding practices, and introduction of complementary foods at 6 months will also be administered at the 9-month and 12-month visits. The rates of adherence will be analyzed. All participants will be included to the final analyses, regardless of having followed the method, since the analyzes will be made by intention-to-treat.

### Outcome measures

*Z*-scores of anthropometric measurements (weight for age, weight for length, length for age, and BMI for age *z*-scores) will be our primary outcome measure to investigate child growth and nutritional status. As secondary outcomes, we will analyze choking prevalence, dietary variety, food and flavor preference, child and parent feeding behavior, iron deficiency, oral hygiene behavior, dental caries, dental development, gingival health status, the prevalence of functional constipation, maternal perception of the CF methods, and prevalence of child eating disorders.

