**Methods/design:**

To evaluate and compare three different complementary feeding methods. Data on 144 mother-child pairs will be randomized into intervention groups by methods: (A) strict Parent-Led Weaning; (B) strict Baby-Led Introduction to SolidS; and (C) a mixed method. Prospective participants from Porto Alegre, Brazil, and nearby cities will be recruited through the Internet. The interventions will be performed by nutritionists and speech therapists, at 5.5 months of age of the child, at a private nutrition office equipped with a test kitchen where meals will be prepared according to the randomized method. The pairs will be followed up at 7, 9, and 12 months of age. Data will be collected through questionnaires designed especially for this study, which will include a 24h child food recall, questionnaires on the child’s and parents’ eating behavior, oral habits, eating difficulties, and choking prevalence. At 12 months of age, children will undergo blood collection to measure hemoglobin, ferritin, and C-reactive protein, saliva collection for analysis of genetic polymorphisms, and oral examination. Anthropometric parameters (child and maternal) will be measured at the baseline intervention, at a 9 month home visit, and at the end-of-study visit at the hospital. The primary outcome will be child growth and nutritional status *z*-scores at 12 months; secondary outcomes will include iron status, feeding behavior, acceptability of the methods, dietary variety, choking, eating behaviors, food preferences, acceptance of bitter and sweet flavors, suction, oral habits, oral hygiene behavior, dental caries, gingival health status, and functional constipation.

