## Methods/design

### Study design

The study will consist of a three-arm controlled trial (Fig. 1), which will intend to randomize mothers and their respective infants into three different groups of CF: (A) strict Parent-Led Weaning (PLW), which is the control arm; (B) strict Baby-Led Introduction to SolidS (BLISS); and (C) mixed method: a combination of PLW and BLISS created especially for this study. Three interventions will be performed throughout the study, and measurement of the main outcomes is expected at 12 months of age. The framework expected to the outcomes is that BLISS and mixed methods will be superior to the PLW method.

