### Sample size

The sample size was calculated using WinPepi® software version 11.65, based on previously published studies on the subject. Considering a unit standard deviation of 1, statistical power of 80%, and a significance level of 5% to detect a difference in BMI of 0.8 kg/m^2^ [18, 24], the sample calculation for a half standard deviation difference will consist of 48 mother-infant pairs for each of the three intervention groups, totaling 144 pairs of mothers and infants.

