### Statistical analysis

The database will be prepared in SPSS (Statistical Package for the Social Sciences) version 21.0, with double entry and validation. Descriptive analyses of continuous and categorical variables will be performed, in the isolated 10% quality assurance sample and in the total sample. Parametric data will be expressed as mean ± standard deviation. All analyses will be conducted by the intention-to-treat principle. The primary analysis will determine whether PLW, BLISS, or the mixed method results in differences in child growth *z*-scores at 12 months of age. Regression analyses will be used to analyze secondary outcomes, including iron intake and status. We will consider adjusting plasma ferritin where there is evidence of infection or inflammation, as indicated by elevated CRP. Statistical significance will be accepted at *p* < 0.05.

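### Four z-scores are jointly primary across three arms at one p < 0.05 threshold, so the chance of a false primary finding exceeds 5%: about 12% to 29%, depending on the test used

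*Protocol article*

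**What the plan says.** - **Primary outcome.** Outcome measures names four z-scores together as the primary outcome: "weight for age, weight for length, length for age, and BMI for age". None is singled out or ranked. The abstract keeps the plural: "The primary outcome will be child growth and nutritional status *z*-scores at 12 months".
- **Primary analysis.** Statistical analysis says: "The primary analysis will determine whether PLW, BLISS, or the mixed method results in differences in child growth *z*-scores at 12 months of age". It does not name the test or say which arms are contrasted.
- **Threshold.** The same section says: "Statistical significance will be accepted at *p* < 0.05". No order of testing, adjustment or requirement that all four succeed is attached to it.
- **Hypothesis.** Study design expects that "BLISS and mixed methods will be superior to the PLW method", which is two comparisons with control for each z-score.
- **Sample size.** The calculation uses 80% power and a 5% level to "detect a difference in BMI of 0.8" kg/m², with SD 1 and a difference of half an SD. It arrives at 48 pairs per arm, 144 in total. No other growth variable enters it.

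**The concern.** With four variables sharing primary status, a significant result on any one of them can be reported as the trial's primary result, and the choice can be made after the data are seen. Three arms multiply the opportunities: four tests if each z-score gets one three-group test, eight if each new method is compared with PLW, twelve if all pairs are compared. A 5% threshold on each test does not then give a 5% chance of a false primary claim. The trial's main conclusion about child growth rests on that claim.

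The sample size adds to the difficulty. It was worked out for one variable at a 5% level, so it leaves no room for a correction over four.

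**Working it through.** **1. Inputs.** From the article: 3 arms, equal allocation, 48 pairs per arm, 4 primary z-scores, significance level 0.05. Assumed: two-sided tests, normal data, and the correlations between z-scores, since the article gives none.

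**2. The plan's own figure.** For two groups, n per arm = 2 × (z for 1 − α/2 + z for 0.80)² / d². With d = 0.5 and α = 0.05: 2 × (1.960 + 0.842)² / 0.25 = 62.8, so 63 per arm. The stated 48 is not reproduced; at 48 the power for 0.5 SD is 68.8%. A one-sided test gives 50 per arm, and a difference of 0.8 with SD 1 gives 25. That mismatch is a separate issue. What matters here is that the calculation covers one variable at an unadjusted 5%.

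**3. If the tests were independent.** Chance of at least one false positive = 1 − 0.95^k.
- k = 4: 18.5%
- k = 8: 33.7%
- k = 12: 46.0%

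The real tests share arms and correlated outcomes, so these figures overstate the error.

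**4. Simulation with no true effect.** 40,000 trials per scenario, 48 per arm, each test at two-sided 0.05. Scenarios A to C assume a correlation of 0.97 between weight-for-length and BMI-for-age, 0.56 to 0.83 between weight-for-age and the others, and the length-for-age with BMI-for-age value shown.

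| Assumed correlations | 4 F-tests | 8 contrasts vs PLW | 12 pairs |
|---|---|---|---|
| A: length–BMI 0 | 12.7% | 21.7% | 28.0% |
| B: length–BMI −0.2 | 13.3% | 22.5% | 29.2% |
| C: length–BMI 0.3 | 11.6% | 20.3% | 26.4% |
| All equal, 0.9 | 9.5% | 16.7% | 21.6% |
| All equal, 0.7 | 13.4% | 22.9% | 29.5% |
| All equal, 0.5 | 15.9% | 26.8% | 34.5% |

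If only differences favouring BLISS or the mixed method count, the eight contrasts give about 11%. If pairs are tested only after a significant F-test on the same z-score, the rate is about 12% for all pairs and 10.5% for contrasts against PLW.

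**5. One primary z-score.** The F-test alone gives 5.0%. Two unadjusted contrasts against PLW give 9.1%, and three unadjusted pairs give 12.2%. Pairs tested only after a significant F-test give about 5% (5.2% simulated). Naming one variable is therefore not enough; the arm comparisons need a rule too.

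**6. Keeping all four, with Bonferroni.** Same formula as step 2, d = 0.5, 80% power, two-sided:
- 0.05/4 = 0.0125: 2 × (2.498 + 0.842)² / 0.25 = 89.2, so 90 per arm
- 0.05/8 = 0.00625: 2 × (2.734 + 0.842)² / 0.25 = 102.3, so 103 per arm
- 0.05/12 = 0.00417: 2 × (2.865 + 0.842)² / 0.25 = 109.9, so 110 per arm

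**The case against.** The strongest reply is that this is a condensed journal article. The choice of test, the contrasts and any multiplicity adjustment are commonly left to an analysis plan, which is not shown. The wording of the primary analysis reads at least as naturally as one three-group test per z-score as it does as eight or twelve separate t-tests. This stands in part. A reader might infer that the plan prescribes eight or twelve unadjusted tests and so carries a false-positive rate of 20% or more. The article does not say so, and those figures hold only if the tests are ungated, unadjusted and count in either direction. The four-variable primary outcome, however, is stated in the text; it is not a detail left out.

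Three further points stand.
- **Direction.** The hypothesis is one of superiority over PLW. Counting favourable differences only, the eight-contrast figure falls by about half. Against this, the primary analysis is worded in terms of differences, and the article does not define which direction of a z-score is favourable.
- **Near-duplication.** It is tempting to say that weight-for-length and BMI-for-age are almost the same measurement at this age. The article gives no correlation, so this remains an assumption. It would also lower the inflation, and the point does not depend on it.
- **Sample-size variable.** A reader might take BMI-for-age z to be the variable used for the sample size. The calculation is in BMI, kg/m², and the Anthropometric measures section lists the two separately. The Background also frames growth faltering in terms of weight or weight gain. Which z-score to name is the investigators' decision.

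**Conclusion.** The point holds. Four z-scores are jointly primary across three arms under one p < 0.05 threshold, with no rule for which result decides the trial. Under scenarios A to C the chance of a false primary finding is about 12-13% with one F-test per z-score, 20-23% with eight contrasts against PLW, and 26-29% with all pairs; it is about 11% for the eight contrasts in the favourable direction only. The lowest two-sided figure in the table, F-tests with all correlations at 0.9, is 9.5%, still nearly double 5%.

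These sizes rest on assumed correlations and on a choice of test that the article does not make, so the range should be cited and not one value from it. Nor does the article promise a family-wise rate of 5%: it states a significance threshold and a sample-size level. The conclusion would change only if all four z-scores had to succeed or an adjustment applied, and the article states neither. It should be settled before analysis because it bears on the main claim.

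**What to change.** Before analysis, name one z-score at 12 months as the single primary outcome and make the other three secondary. BMI-for-age z is the natural candidate, as the listed variable closest to the BMI used for the sample size, though not identical to it; the reason for the choice should be given.

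For the three arms, use one of two rules:
- Do the three-group F-test at 5% and test pairs at 5% only if it is significant. With exactly three groups this holds the family-wise error at 5%.
- Test only the two contrasts against PLW, adjusted by Holm or Dunnett. This fits the stated hypothesis more directly.

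If all four z-scores are to stay primary, state the multiplicity adjustment or the success rule, and restate the power. Under Bonferroni, 0.5 SD at 80% power needs 90 to 110 pairs per arm, against the planned 48.

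**Cost.** No extra participants or measurements under a single primary outcome. Three z-scores lose primary status, and pairwise claims become gated or adjusted. Because Trial status gives 14/03/2019 as the start of recruitment, the change has to be recorded in the registry as a dated amendment, with a statement that it was made without sight of outcome data by arm, if that is so.

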### Anthropometric measures

The first questionnaire, administered at 6 months, will inquire about birth weight, birth length, and head circumference. Mothers are expected to obtain these data from the child’s hospital records or vaccination card.

At 6, 9, and 12 months of age, blinded researchers trained by the International Society for the Advancement of Kinanthropometry (ISAK) [62] will obtain anthropometric measurements, double-checking and calculating a mean value for every assessment. Inter-observer technical error of measurement (TEM) [63] and the coefficient of reliability will be calculated, and anthropometry standardization sessions will be conducted to monitor the measurement techniques and prevent error or bias. Teams will be retrained throughout the study as necessary.

All infant participants will be weighed completely undressed and diaperless, in the laps of their mothers, who will be expected to wear light clothes only (no shoes, cellphone, wallets, or other accessories). The mothers will then be weighed alone, and the latter result subtracted from the former to obtain the child’s weight. We intend to use calibrated digital scales (Plenna®) with 0.1 kg resolution.

Recumbent length will be measured to the nearest 0.1 cm using a portable length board. The same calibrated equipment will be used at every phase of the study to ensure accuracy. All measurements will be taken in duplicate and the average calculated. BMI (kg/m^2^) and BMI-for-age (*z*-score) at 6, 9, and 12 months of age, as well as weight-for-age, weight for length, and length for age *z*-scores, will be calculated using the WHO child growth standards [16].

Skinfolds (triceps and subscapular) will be measured with a calibrated adipometer (Lange®) in mothers and infants, as well as arm and waist circumference in mothers and head and arm circumference in children.

### Questionnaires

Upon study enrollment, mothers will complete a sociodemographic questionnaire for calculation of the Brazilian Index Score (ABIPEME criteria) [64].

At 9 and 12 months, we will investigate feeding practices and the presence of choking. Eating behaviors and intestinal habits will be inquired specifically at the 12-month visit, as will the acceptability of the allocated CF approach to parents, focusing on “mess”, convenience, and cost.

Food intake will be assessed by a 24-h dietary recall. Data on oral hygiene habits will be collected through a questionnaire created for this study. Infant feeding behavior will be tested by the Baby Eating Behavior Questionnaire (BEBQ) [65] and Children Eating Behavior Questionnaire (CEBQ) [66]. Parental feeding perception will be assessed by the Caregiver Feeding Style Questionnaire (CFSQ) [67], while parental eating behavior will be assessed by the Dutch Eating Behavior Questionnaire (DEBQ) [68]. Finally, eating difficulties will be assessed with the Montreal Children’s Hospital Eating Scale (MCH-FS) [69].

### Choking

At the 9-month and 12-month visits, choking and gagging will be assessed by specific questions regarding frequency, a description of which food or drink and consistency was involved, how many times it occurred and maneuvers used to resolve the episode. Researchers will be trained to make sure they are able to distinguish a gagging event from a choking event while applying the questionnaire. We also hope the video examples shown to participants during the first intervention will help them distinguish between the two when reporting events to the researchers.

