#### Adverse events

We intend to monitor any adverse event caused by the trial participation. Presence of choking incidents will be identified in the questionnaires along with possible growth faltering, identified during the 9- and 12-month anthropometric measurement sessions. We will pay special attention to monitor multiple occurrences of adverse events in a specific participant as well as a high prevalence of any adverse event in multiple participants.

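### Choking is first asked about at 9 months, so events in the first month of solids are recalled after 2 to 3 months, although families are already phoned at 7 months

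*Protocol article*

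**What the plan says.** Solids are timed in the advice common to all groups (Study groups, text under Table 1). Mothers are told: "Not to start CF until their infant is 6 months of age". Feeding then builds up quickly: "At age 6 months, offer a fruit at two different times plus one main meal (lunch) and, by 7 months, introduce a second main meal".

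The choking questions are timed in two places, which agree. The Questionnaires section says: "At 9 and 12 months, we will investigate feeding practices and the presence of choking". The Choking section says: "At the 9-month and 12-month visits, choking and gagging will be assessed by specific questions regarding frequency". It goes on to ask for the food or drink and its consistency, the number of occurrences and the manoeuvres used.

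The Adverse events section relies on the same instruments: "Presence of choking incidents will be identified in the questionnaires along with possible growth faltering, identified during the 9- and 12-month anthropometric measurement sessions". It also undertakes to look for repeated events in one participant and for a high prevalence across participants.

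There is a contact between the start of solids and the 9-month visit. The Adherence section says: "a blinded researcher will conduct a phone call when the child is 7 months of age and ask some key questions". The questions listed there are "about food consistency when the child started to eat, and at 7 months; if the child takes food to mouth alone", together with whether the child is fed by spoon. Choking is not among them. The Abstract gives follow-up at 7, 9 and 12 months. Choking prevalence is a secondary outcome under Outcome measures.

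**The concern.** Choking is the safety question that the protocol itself raises about baby-led feeding, in the Background and in its own Choking subsection there. The data requested are detailed: how often, with which food, in what consistency, and how it was resolved. Mothers must also separate choking from gagging, helped by videos shown when the child was 5.5 months old. Detail of this kind is harder to give after two or three months than after a few weeks. The mothers who give it know their group, so differential reporting by arm is possible, although nothing in the document indicates its direction or size.

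The second consequence concerns timing. The Adverse events section undertakes to notice clusters within a child and across children. If choking reaches that review only through questionnaires given at 9 and 12 months, a cluster in a child's first weeks of solids becomes visible through a structured question only at that child's 9-month visit. An existing contact at 7 months, already about feeding method, is not used for this.

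**Working it through.** The protocol gives no figure to reproduce here, so the check is date arithmetic on its own time points.

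**Inputs**
- Advised start of solids: 6 months (Study groups, text under Table 1).
- Phone call: 7 months (Adherence).
- Choking questions: 9 and 12 months (Questionnaires; Choking).
- End of follow-up: 12 months (Abstract).

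**Time before the first structured question**
- 9 − 6 = 3 months.
- Share of the feeding period up to 12 months: 3 / (12 − 6) = 0.5.

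**Recall interval** = age when asked − age at event.

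| Age at event (months) | As written | With the items added at 7 months |
|---|---|---|
| 6–7 | 9−7 to 9−6 = 2–3 months | 7−7 to 7−6 = 0–1 month |
| 7–9 | 9−9 to 9−7 = 0–2 months | 0–2 months (unchanged) |
| 9–12 | 12−12 to 12−9 = 0–3 months | 0–3 months (unchanged) |

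The gain is confined to the first month of solids. For events spread evenly over that month, the mean recall interval falls from 2.5 to 0.5 months.

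**What the interval might mean for capture (assumption only).** The document gives no rate of forgetting. Suppose a fraction d of events is forgotten per month, so that an event is reported after delay t with probability (1 − d)^t. Averaged over delays from a to a + 1 months, this is [(1 − d)^a − (1 − d)^(a+1)] / [−ln(1 − d)].

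| Assumed d | Asked at 9 months (a = 2) | Asked at 7 months (a = 0) |
|---|---|---|
| 0.1 | (0.810 − 0.729)/0.105 = 0.77 | 0.100/0.105 = 0.95 |
| 0.2 | (0.640 − 0.512)/0.223 = 0.57 | 0.200/0.223 = 0.90 |
| 0.3 | (0.490 − 0.343)/0.357 = 0.41 | 0.300/0.357 = 0.84 |

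These are probabilities for a single event. The listed outcome is prevalence, and a child counts if any one event is recalled. If a child had, say, three events and each were recalled independently with probability 0.57, the child would be counted with probability 1 − 0.43³ = 0.92. The per-event table therefore overstates the loss in prevalence. It bears more directly on counts and on the description of each event.

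**The case against.** **The sections agree, and the whole period is covered.** This stands. There is no contradiction between the Questionnaires, Choking and Adverse events sections. The 9-month visit asks about events since solids began, so 6 to 9 months is collected, though retrospectively.

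**Other routes exist before 9 months.** This also stands. A reader might infer that choking is not monitored for safety at all in the first three months of solids, or that clusters cannot be noticed before 9 months. The document does not support that. The Adverse events section states a general intention to monitor adverse events caused by participation. Every mother has a dietitian's telephone number for questions, and Quality control provides for individual evaluation of unexpected situations. These routes depend on the mother or on chance, and none is a choking query, but they are not nothing.

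**A 7-month item may exist.** Neither section says that choking is asked at no other time. The article is condensed, the Adherence section gives key questions and not a full call script, and Table 1, the schedule of measures, is not shown in the text reviewed. A 7-month item cannot be excluded. No text points to one, however. The Abstract names follow-up ages and instruments without linking them, and the 24-hour recall in the same list is placed at 9 and 12 months under Dietary assessment.

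**The recall loss is unproven.** This stands. The monthly rates above are assumed, apply equally to mild and serious events, and describe single events. A choking episode that needed a manoeuvre is probably remembered better than a minor one.

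**The remedy is partial.** This is true. The 9-to-12-month interval is unchanged, and mothers know their group at 7 months too. The remedy shortens recall for the month in which it is longest for every event.

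**Conclusion.** The point holds as a matter of timing. On the text, the first structured choking question comes 3 months after the advised start of solids, halfway through the 6 months of feeding studied. Events at 6 to 7 months are recalled after 2 to 3 months, although a 7-month call is already planned. The result is later and less precise capture of a secondary outcome, and a later structured input to the adverse-event review.

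The conclusion rests on three assumptions: families start solids at about 6 months as advised, the 7-month call reaches all families, and Table 1 holds no 7-month choking item. The loss in recalled events is unknown, and the illustration above should not be cited as an estimate. The primary outcome, growth z-scores at 12 months, is not affected. This is a cheap improvement of optional to moderate priority.

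**What to change.** First check Table 1 and the call script. If choking is already asked at 7 months, the Questionnaires, Choking and Adverse events sections need only be brought into line with them.

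If it is not:
- Add the existing choking and gagging items (frequency, food and consistency, number of occurrences, manoeuvre used) to the 7-month call.
- Give the caller the same training in telling choking from gagging that the Choking section requires of the researchers at the visits.
- Forward positive answers to the review described under Adverse events.
- Have the 9-month visit ask about the period since the call, or since the start of solids for families not reached at 7 months. Choking can then be tabulated for 6–7, 7–9 and 9–12 months without double counting.

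The cost is a form revision, a few more minutes per call and brief training, with no new visit or staff. The caller already asks about spoon use and self-feeding, so little further blinding is at risk. There is a small chance that asking about choking one month into solids prompts some families to change how they feed. The same items should therefore be asked in the same words in all three groups. Recall for 9 to 12 months stays at up to 3 months.
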